##### Gradior Cognitive

This small-scale pilot study will be conducted by INTRAS in Valladolid, Spain. The objective of this small-scale pilot study is to assess the most recent functionalities of Gradior Cognitive (Figure 3) by exploring the usability and preliminary effectiveness of the new features oriented to support the therapists and by assessing user experience and satisfaction in older adults with MCI. Data will be collected at two time points: at baseline and immediately after the end of the intervention.

**Figure 3 figure3:**
[figure not shown]
Gradior Cognitive screenshots.

Outcome measures and general feedback will be collected from therapists ([clinical] psychologists, neuropsychologists, and gerontologists) using the new version of Gradior Cognitive (N=6 to 10). Furthermore, approximately 30 older adults with MCI will be recruited from the INTRAS Memory Clinic and Neuropsychological Rehabilitation Center in Valladolid, Spain. Potential older participants will be screened (cognitive abilities) before study participation. The inclusion criteria include the following: patients aged ≥55 years; patients with willingness and ability to collaborate in the study; and patients with either (1) a Mini-Mental State Examination [58] score of ≥21 and ≤27 indicating MCI according to the Petersen criteria for MCI-amnestic [59] and the international working group on MCI-amnestic or (2) initial dementia as categorized by the Diagnostic and Statistical Manual of Mental Disorders, fifth edition, and a Clinical Dementia Rating of ≥1 and ≤2 and a Geriatric Depression Scale score of <5 [60]. The exclusion criteria include the following: hearing or visual impairments (inability to use the devices); psychiatric, neurological, or nutritional condition preventing the individual from participating in the study; having a history of substance abuse (alcoholism or alcoholic-type dementia); and being on antipsychotic medication.

Gradior Cognitive is a neuropsychological evaluation and rehabilitation software for the implementation of higher cognitive function training programs for people with cognitive deficit or impairment. Gradior Cognitive allows working on attention, perception, orientation, memory, calculation, executive function, language, and reasoning in adults. The system consists of a website (intended for professionals) and an app for users to conduct intervention sessions. It analyzes and updates the results obtained reporting on users’ performance in different cognitive areas, proposing changes in the session plan. This software supports therapists in the early detection and monitoring of cognitive impairment, also enabling a personalized cognitive rehabilitation program for improvement or maintenance of cognitive skills. Participant therapists included in the study will be using the new Gradior Cognitive features on a daily basis for at least two months. Individual interviews will be conducted to gather details on the therapist’s experience and assess usability and perceived effectiveness. For the older adult participants, the adopted intervention consists of 2-weekly sessions of 30 minutes using Gradior Cognitive for a period of 4 to 6 months. Sessions will be supervised by experienced Gradior professionals.

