#### Technological Innovations in a Rehabilitation Context

For this study (JRA), we will focus on the use of technology for rehabilitation in patients with stroke and people living with mild cognitive impairment (MCI; in accordance with the expertise and available infrastructures of the involved living labs). Stroke is a leading health problem, and its burden is increasing worldwide [8]. Similarly, the prevalence of dementia, a neurodegenerative condition with a high physical, psychological, social, and economic impact for both patients and their carers, is rising sharply [9]. MCI is an intermediate state between normal cognition and dementia with preserved functional abilities [10]. Accumulating evidence supports the use of technology during the rehabilitation process both on a cognitive level and on a physical level. Concerning cognitive rehabilitation, García-Casal et al [11] have shown that computer-based cognitive interventions for people living with dementia lead to (moderate) beneficial effects on cognition, depression, and anxiety. For example, Gradior cognitive rehabilitation is a computer-based program for neuropsychological assessment and cognitive stimulation in healthy individuals as well as for neuropsychological rehabilitation in people with one or more cognitive disorders [12]. Concerning physical rehabilitation, a wide variety of technologies have been proposed, for example, virtual reality (VR), technologies for remote rehabilitation (telerehabilitation), technologies for augmenting gait training, and a short-arm human centrifuge (SAHC) for gravity therapy. A growing body of evidence supports the use of VR for rehabilitation of different pathologies. The benefits of using VR during the rehabilitation process of patients with stroke, patients with cerebral palsy, patients with spinal cord injuries, and other pathologies include improvements in balance and gait [13] and motor functions, greater community participation, and improved psychological and cognitive function [14]. With advances in information and communication technologies, telerehabilitation has gained increased research interest, as it allows rehabilitation services to be provided to patients remotely in their homes or elsewhere [15]. Research has shown that the effectiveness of telerehabilitation for patients with stroke is similar to that of traditional face-to-face rehabilitation but that different stakeholders have different opinions on the subject [16]. Patients are satisfied with telerehabilitation provided that it is appropriate and some social interaction occurs, whereas clinicians prefer face-to-face interactions and will only use telerehabilitation when face-to-face interactions are not feasible [16]. Another example of a promising technology for physical rehabilitation is the use of a split-belt treadmill for balance and gait training in patients with stroke [17,18]. Finally, gravity therapy by means of a SAHC, an integrated multisystem countermeasure to provide artificial gravity training for rehabilitation purposes, has been proposed to have beneficial effects for individuals with neuromuscular disorders, balance disorders, stroke, and sports injuries. By simulating natural gravity, it targets physiological deconditioning imposed by inactivity or a lack of gravitational force. It functions by exerting a centrifugal force on a body accelerated centripetally in a rotating device [15]. However, more research is needed to be able to provide a personalized therapy [19,20].

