**INTRAS**				
	**Gradior Cognitive**			
		Neuropsychological or cognitive assessment	Screening: Montreal Cognitive Assessment [53], Gradior Cognitive	
		Performance characteristics	Gradior Cognitive: % successes, graded cognitive performance scores, mistakes and successes by commission, mistakes by omission, number of performed sessions	

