A total of 12 to 15 patients with stroke will be recruited from the stroke unit of the 2 sites for each locomotor training protocol. Participants will be selected for their potential to improve gait capacities and according to the requirements of their individual goals for improvement. The inclusion criteria will be the following: (1) having a first unilateral stroke and being in rehabilitation, (2) having initiated the gait training with or without assistive devices, (3) tolerating 1 hour of exercise with breaks, (4) in the presence of aphasia showing no more than mild or mild to moderate impairment, (5) having a reliable yes and no. The exclusion criteria will include cerebellar lesions, major pain, hemineglect or hemianopsia, signs of major depression quantified with a score of ≥10 out of 15 on the Geriatric Depression Scale [63], severe cognitive deficits defined with a score of <25 out of 30 on the Mini-Mental State Examination developed by Folstein et al [64], cardiorespiratory problems, and other medical and cognitive conditions that could affect the ability to understand instructions, as verified by medical records. We will also collect data on usability, feasibility, and opinions from clinicians about the training interventions through questionnaires or interviews.

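### The Gradior pilot is described as a study of older adults with MCI, but its second entry route admits dementia, so results for the whole group cannot be assumed to describe MCI

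*Protocol article*

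**What the plan says.** **Stated population.** In the Gradior Cognitive section, the part of the objective that concerns patients is to be met "by assessing user experience and satisfaction in older adults with MCI". The recruitment sentence gives the number and the label: "approximately 30 older adults with MCI will be recruited from the INTRAS Memory Clinic and Neuropsychological Rehabilitation Center". The Methods paragraph of the Abstract and the section Site Selection, Sample, and Recruitment also name only two patient groups for the whole project, stroke and MCI.

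**Entry criteria.** The inclusion criteria in the Gradior section are joined by either/or. Route 1 is a Mini-Mental State Examination "score of ≥21 and ≤27 indicating MCI according to the Petersen criteria for MCI-amnestic" and a working-group definition. Route 2 is "initial dementia as categorized by the Diagnostic and Statistical Manual of Mental Disorders, fifth edition, and a Clinical Dementia Rating of ≥1 and ≤2", with a depression-scale condition added.

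**Definition.** The Introduction (Technological Innovations in a Rehabilitation Context) states that "MCI is an intermediate state between normal cognition and dementia with preserved functional abilities".

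**Elsewhere.** Study Significance, in the Discussion, describes the project's secondary outcome as concerning stroke and people living with MCI or dementia. The Data Analysis section for Phase 2 describes a general repeated-measures approach and lets each pilot vary it. It mentions no split by diagnosis.

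**The concern.** The objective and the recruitment sentence say whom the results are about, and the criteria say who gets in. Here they differ. A site that follows the criteria exactly can enrol people with dementia and then report on them as older adults with MCI.

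The article presents the Gradior patients as one group measured at baseline and at the end of the intervention. If that group mixes two diagnoses in unknown proportion, a usability score, a satisfaction score or a before-after change belongs to the mixture. Whether it also holds for MCI depends on two things that the article does not give: how many participants enter by each route, and how far the two groups differ on each outcome. The label on the results would then claim more than the design supports, on the outcomes that this pilot mainly exists to produce.

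**Working it through.** The article gives no power or effect figure for this pilot, so there is nothing of that kind to reproduce. The check is a comparison of texts, followed by simple arithmetic on the unknown mix.

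**Step 1. Set the texts side by side.**
- Label: older adults with MCI (Gradior objective and recruitment sentence; Abstract and Site Selection name MCI and not dementia).
- Definition: MCI lies between normal cognition and dementia, with function preserved (Introduction).
- Route 2: "initial dementia as categorized by the Diagnostic and Statistical Manual of Mental Disorders, fifth edition", with a Clinical Dementia Rating from 1 to 2.

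By the definition, someone with dementia is past the MCI state. Route 2 is an alternative to route 1, not a further condition on it. A participant can therefore meet the criteria without having MCI.

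**Step 2. Range of the mix.** Inputs: n = 30 (Gradior section); k = number entering by route 2, which is not given. No cap or quota is stated, so k can be anything from 0 to 30.

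**Step 3. Effect on a combined mean.** Let D be the difference between the dementia mean and the MCI mean on some outcome. Then

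combined mean = [(30 − k) × MCI mean + k × dementia mean] / 30 = MCI mean + (k/30) × D.

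D is not given, so the shift is expressed as a share of D.

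**Step 4. Effect on the usability sample.** Site Selection, Sample, and Recruitment justifies about 15 participants per pilot by detection of up to 90% of usability problems. For illustration, assume that every problem has the same chance p of being met by each participant, independently. Taking 90% at 15 participants:

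1 − (1 − p)^15 = 0.90, so p = 1 − 0.1^(1/15) = 0.142.

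Detection among the m = 30 − k MCI participants alone is then 1 − (1 − p)^m.

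| k (route 2) | MCI participants | Shift of combined mean, k/30 of D | Detection among MCI alone |
|---|---|---|---|
| 0 | 30 | 0% | 99.0% |
| 5 | 25 | 17% | 97.8% |
| 10 | 20 | 33% | 95.4% |
| 15 | 15 | 50% | 90.0% |
| 20 | 10 | 67% | 78.5% |
| 25 | 5 | 83% | 53.6% |
| 30 | 0 | 100% | 0% |

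Up to k = 15, the MCI subset still meets the article's usability target by itself. Above 15 it does not.

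**The case against.** **Dementia may be intended.** The Discussion speaks of MCI or dementia, and the Gradior section describes the software as meant for people with cognitive deficit or impairment generally. The fault may then lie in an incomplete label and not in the criteria. This stands, and it is why simply deleting route 2 is not clearly right. It leaves the article naming two different target populations.

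**The detail may be elsewhere.** Strata and separate reporting are commonly left to a full protocol or analysis plan, and neither is shown. Pooling is inferred from the single group of about 30. It is not stated, and the Data Analysis section allows each pilot its own approach. This also stands: the absence of a planned split is not in itself the fault. But a later document could separate the groups without making a dementia patient fit an MCI label, and that conflict is in the text shown.

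**Stronger readings that the documents do not support.**
- A reader might infer that the results will fail to describe MCI. Route 2 permits dementia entrants but does not ensure them, and k could be 0.
- A reader might infer that opposite changes in the two groups would cancel. The article gives no effect in either group, so any such example is invented.
- A reader might see a contradiction between Table 2, which lists "Screening: Montreal Cognitive Assessment", and eligibility by the Mini-Mental State Examination. Nothing says that the first test decides entry, and a study may use both.
- A reader might set Gradior's MCI range against the augmented gait pilot's exclusion of "severe cognitive deficits defined with a score of <25 out of 30 on the Mini-Mental State Examination". That is an exclusion for stroke patients, for a different purpose, and no result depends on the wording. Gradior's route 1 also does not rest on the score alone.

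**Conclusion.** The point holds as a conflict between a stated population and a stated rule. The article calls the Gradior patients older adults with MCI, admits dementia by an alternative route, defines MCI so as to exclude dementia, and names both groups in the Discussion.

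The consequence is conditional. Between 0 and 30 of the 30 may have dementia, and a combined mean would sit k/30 of the way from the MCI mean to the dementia mean. That is a third of the difference at 10 route 2 entrants and half at 15. Beyond 15, fewer than 15 MCI participants remain. Under the equal-chance assumption, detection among 10 of them would be about 78%, against the article's figure of up to 90%.

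Three assumptions carry this. The route 2 share is unknown and taken over its full range. The group would be summarised as one, which is inferred. The two diagnoses differ on the outcomes, by an amount that the article does not give; if they did not differ, the combined mean would not be displaced. The pilot is small and exploratory, so this limits what can be concluded from it and does not invalidate it.

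**What to change.** Reconcile the population named in the Abstract, in Site Selection, Sample, and Recruitment, and in the Gradior objective and recruitment sentence with the Gradior entry criteria and with the Discussion.

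If both routes are kept:
- name both populations in the objective and in the sample description;
- record the entry route of each participant;
- report usability, satisfaction and before-after change by route;
- make no statement about MCI from the combined group.

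If the sponsor intends MCI only, the criteria and the Discussion should be brought into line with that.

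The cost is a change of wording and one recorded item per participant. Reporting by route means smaller groups and less precision in each. Restricting entry to MCI would cost recruitment by an amount that cannot be judged, because the expected share of route 2 is not given.

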##### VR Mirror Therapy

This small-scale pilot study will be conducted by LiCalab-Mobilab & Care in Belgium. Mirror therapy is a rehabilitation method during which a mirror is placed between the arms or legs of a patient to create the illusion that a patient’s affected limb is moving when the patient sees his or her unaffected limb moving in the mirror. The objective is to assess the noninferiority of VR mirror therapy as compared with standard mirror therapy in patients with subacute and chronic stroke, as well as to assess user experience of the VR mirror therapy from the perspective of both patients and clinicians. To do so, a two-arm, unblinded, randomized, controlled, parallel design is adopted to compare VR mirror therapy to regular mirror therapy (treatment as usual) in patients with stroke. A total of 20 patients with stroke will be randomly assigned to either the VR group or the control group receiving mirror therapy as usual. Data will be collected at four time points: at baseline, immediately after the first intervention session, before the last intervention session, and immediately after the last intervention session.

A total of 20 patients with stroke will be recruited by clinicians in partner rehabilitation centers or rehabilitation departments of general hospitals in Belgium and will be randomized to VR mirror therapy or treatment as usual. The clinicians themselves will also participate in the study by contributing data on usability and feasibility. The inclusion criteria for patients include the following: patients with stroke in the subacute or chronic phase, aged 18 to 85 years, with normally functioning upper limb on the nonaffected side and impaired functioning of the upper limb on the affected side, with the ability to sit independently on a chair or in a wheelchair in order to freely move the (unaffected) upper limb, and with the ability to follow verbal instructions. The exclusion criteria for patients include the following: patients with acute stroke, medically unstable patients, patients with visual deficits interfering with the execution of activities of daily living, patients with allergies for materials used on the VR headset (eg, silicone), patients with epilepsy, patients who have extreme sensitivity to motion sickness, and patients with facial wounds or lesions impairing the use of the VR headset.

Using an Oculus Quest VR headset (Meta) with built-in hand tracking, participants will be immersed in a VR kitchen and garden, where they will perform various actions in order to successfully complete a cooking program (Figure 4). These actions must be performed (in reality) by the side of the body that is unaffected by the stroke and include only upper-limb activities of daily living such as grasping ingredients or kitchen utensils, cutting vegetables, putting ingredients in a cooking pot, and stirring in the cooking pot. The movements of the unaffected side are projected to the affected side (mirrored), so that the patient appears to be performing the actions with the affected side. Participants in the control group will perform standard mirror therapy. Both groups will be administered the assigned therapy once per week over a period of 8 weeks.

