### Study Aims and Objectives

VITALISE aims to harmonize living lab procedures and open living lab infrastructures as a means to facilitate and promote research activities in the health and well-being domain in Europe and beyond. With this JRA, we primarily aim to gain insight into each living lab’s infrastructure and procedures to harmonize health and well-being living lab procedures and infrastructures, particularly in the context of rehabilitation. Secondarily, we aim to investigate the potential of innovative technologies for rehabilitation through living lab methodologies. To do so, multiple international living labs will organize cocreation sessions with patients and care professionals to capture stakeholder perspectives on rehabilitation technology (phase 1) and organize separate small-scale pilot studies to test 6 innovative intervention or data collection technologies in practice using preliminary harmonized procedures (phase 2). The living lab research activities have the following objectives: (1) to assess how different stakeholders across multiple countries view the role of technology in rehabilitation; (2) to collect suggestions regarding specific rehabilitation innovations (phase 1); (3) to perform small-scale pilot studies providing insights into end user experiences and usability of 6 selected cognitive and motor rehabilitation interventions; and (4) to explore the effects of these pilot interventions through self-report, physiological, and motor data of small samples (phase 2).

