### Site Selection, Sample, and Recruitment

Study phases 1 and 2 will be conducted by each living lab; therefore, recruitment will be carried out at each living lab’s partner rehabilitation centers, rehabilitation departments of hospitals, or transitional living facilities in the context of rehabilitation across Europe and Canada. Participants will include patients with stroke or individuals with MCI (depending on the technology of interest and the planned small-scale pilot study).

In phase 1 (cocreation), approximately 4 to 12 participants will be included per session in accordance with guidelines for group sessions [25,26]. In phase 2 (small-scale pilot studies), each pilot aims to include approximately 15 participants, as previous research has suggested that this sample size is sufficient to detect most usability problems (up to 90%) [27,28]. Note, however, that the exact numbers can differ among the test sites depending on partner-specific objectives and methods.

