#### Small-Scale Pilot Studies (Phase 2)

Best practices for analyses will be exchanged among partners to ensure a harmonized approach and the generalizability of the findings. However, for each small-scale pilot study, the statistical approach might vary according to the needs of the respective study. In general, descriptive statistics will be presented for demographic information. For quantitative data, normal distribution will be tested. The effects of an intervention on dependent variables will be assessed over time (eg, before-after, follow-up sessions) using repeated-measures parametric or nonparametric tests. The effect sizes of changes found among evaluations will be computed. The significance level is set at *P*<.05.

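### The VR mirror therapy pilot names noninferiority as an objective, but 20 patients cannot dependably support it and nothing else in the article is built for it

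*Protocol article*

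**What the plan says.** Four parts of the Protocol article bear on this point.

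- **VR Mirror Therapy (objective and design).** The first-named objective is "to assess the noninferiority of VR mirror therapy as compared with standard mirror therapy in patients with subacute and chronic stroke"; user experience of patients and clinicians comes second. To serve these aims, "a two-arm, unblinded, randomized, controlled, parallel design is adopted to compare VR mirror therapy to regular mirror therapy". On size: "A total of 20 patients with stroke will be randomly assigned to either the VR group or the control group". No allocation ratio is given.
- **Site Selection, Sample, and Recruitment.** The phase 2 rationale is generic: "each pilot aims to include approximately 15 participants, as previous research has suggested that this sample size is sufficient to detect most usability problems". The section adds that numbers may differ by site according to each partner's objectives and methods. No separate reason is given for 20 in the VR pilot.
- **Data Analysis, Small-Scale Pilot Studies (Phase 2).** The general approach is repeated-measures parametric or nonparametric tests of effects over time, with effect sizes. "The significance level is set at *P*<.05". The section allows the statistical approach to vary by pilot.
- **Study Aims and Objectives.** The fourth objective is "to explore the effects of these pilot interventions through self-report, physiological, and motor data of small samples".

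**The concern.** Noninferiority is a specific claim: the new treatment is not worse than the comparator by more than a set margin. It is supported when a confidence interval for the between-arm difference excludes that margin, so it depends on precision. Twenty patients give little precision, and the article's sizing argument concerns the number of users needed to uncover usability problems, which says nothing about comparing two arms.

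In a superiority trial, too few patients mostly leads to a missed effect. Where the hope is to find no important difference, too few patients produce a nonsignificant result almost whatever the truth, and that can be mistaken for support. What is at stake is whether the pilot's first-named objective can be answered by its design, and whether its result could be read as a reason to use VR in place of standard mirror therapy.

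**Working it through.** **Inputs from the article.** 20 patients, two parallel randomized arms, significance level .05 (sidedness not stated).

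**Assumptions.** 1:1 allocation, so n = 10 per arm, the most favourable split; a continuous outcome with common SD; no dropout; true difference zero for power; one-sided 2.5% unless noted. The article gives no margin, SD or target power, so results are in SD units over a range of margins.

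**1. The plan's own figure.** N = 20 cannot be reproduced as a noninferiority sample size, because no inputs for one are given. The stated rationale can be checked only as problem discovery, 1 − (1 − p)^n. With n = 15 this reaches 90% when each problem affects a proportion p = 0.142 of users. The article states no p, and the calculation has no bearing on a between-arm difference.

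**2. Precision.** Half-width of the 95% confidence interval = t(0.975, 18 df) × √(2/n) = 2.101 × √(2/10) = 2.101 × 0.447 = 0.94 SD. For a 90% interval: 1.734 × 0.447 = 0.78 SD.

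**3. Power, unadjusted.** Noncentral t with 18 df and noncentrality margin/√(2/10):

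| Margin (SD) | Noncentrality | Power, one-sided 2.5% | Power, one-sided 5% |
|---|---|---|---|
| 0.3 | 0.67 | 9% | 16% |
| 0.5 | 1.12 | 18% | 28% |
| 0.75 | 1.68 | 36% | 49% |
| 1.0 | 2.24 | 56% | 69% |

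80% power needs a margin of about 1.33 SD at one-sided 2.5%, or 1.16 SD at one-sided 5%.

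**4. Patients needed.** Normal approximation, n per arm = 2(1.960 + 0.842)²/margin², at 80% power and one-sided 2.5%. Margin 0.5 SD: 2 × 7.85/0.25 = 62.8, so 63 per arm. Margin 1.0 SD: 15.7, so 16 per arm.

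**5. Power with baseline adjustment.** ANCOVA multiplies the residual SD by √(1 − r²), where r is the baseline-to-final correlation (assumed). One-sided 2.5%, 17 df:

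| r | √(1 − r²) | 95% half-width (SD) | Power, margin 0.5 SD | Power, margin 0.75 SD | Power, margin 1.0 SD |
|---|---|---|---|---|---|
| 0.7 | 0.714 | 0.67 | 32% | 60% | 84% |
| 0.8 | 0.600 | 0.57 | 42% | 75% | 94% |
| 0.9 | 0.436 | 0.41 | 68% | 95% | >99% |

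**6. What a nonsignificant result would mean.** Chance of P>.05 in an unadjusted two-sided t test, 10 per arm, when VR is truly worse:

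| True deficit (SD) | P(nonsignificant) |
|---|---|
| 0.3 | 90% |
| 0.5 | 81% |
| 0.8 | 60% |
| 1.0 | 44% |

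P>.05 is thus the usual result even when VR is worse by half an SD.

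**The case against.** **The analysis is not fixed.** The phase 2 analysis text is a general default, it speaks of tests over time, and it lets each pilot vary its approach. A .05 level is compatible with a noninferiority test, which also has an alpha. An endpoint, margin and interval rule may stand in a fuller pilot protocol or analysis plan that is not shown. All of this stands. A reader might infer that the pilot will judge noninferiority by a between-arm difference test at P<.05; the article does not say so. The nonsignificance figures describe what such a reading would be worth, not what is planned. The missing margin is not the point either: the size is stated in the article, and a margin set elsewhere would not change the precision that 20 patients give.

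**The size is not hopeless under every assumption.** A reader might infer that 10 per arm can exclude no plausible margin. The documents do not support that: they give no margin or SD, and with baseline adjustment a 1.0 SD margin has 84% power or more at r of 0.7 and above. This stands, and it limits the conclusion to dependable reach rather than impossibility.

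**The programme is exploratory and the objective says assess, not show.** It is fair to resist calling the objective confirmatory, or predicting that the result will be misreported; neither is in the text. But the exploratory framing in the study aims is a reason to bring the pilot's objective into line with it, not a reason to leave a margin-based term in place.

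**Randomization.** Chance imbalance between subacute and chronic patients might also be raised. The article states neither the expected mix nor whether the list is stratified, so no finding follows.

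**Conclusion.** The concern holds as a mismatch between one stated objective and the rest of the article. The VR pilot's noninferiority aim does not fit its 20 patients, the usability-based sizing rationale, the general analysis default or the exploratory aim for phase 2.

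Unadjusted power is 18% at a 0.5 SD margin and 56% at 1.0 SD. Baseline adjustment lifts the 0.5 SD figure to between 32% and 68%. Dependable power requires a wide margin or a very high baseline correlation, and the article gives no basis for either. These figures rest on assumed 1:1 allocation, no dropout, equal true means, and assumed margins and correlations. An uneven split or any dropout would lower them.

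The user experience objective is unaffected.

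**What to change.** In the VR Mirror Therapy section, replace the noninferiority objective with one that matches the study aims: to estimate the between-arm difference in arm function (for example Fugl-Meyer, adjusted for baseline by ANCOVA) with a 95% confidence interval, to inform a later noninferiority trial. State that no noninferiority conclusion will be drawn from this pilot, and that P>.05 is not evidence of noninferiority. Keep user experience as the objective that this size supports. Fugl-Meyer is offered only as an example, since the article lists it beside pain and range of motion without naming a lead outcome.

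The cost is the wording of one objective and an added analysis sentence, with no extra patients or visits. The downside is a less ambitious claim. If the sponsor prefers to keep noninferiority, the alternative is to name an endpoint and a justified margin and to size the trial for it; at a 0.5 SD margin that is 63 per arm unadjusted, or about 33 per arm with an assumed baseline correlation of 0.7 (63 × (1 − 0.49) = 32.1, rounded up).
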